#### Intervention adherence

The use of the app will be assessed and recorded including number of times the app is used, for how long, and progress through the different modules. A minimum intervention dose for the app will be defined a priori, with “compliance” defined as completion of a pre-specified minimum level of usage of the unguided self-help intervention (at least 2 modules of 7 modules in treatment package). All participants in the usual practice control will be defined as receiving the minimum intervention dose.

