### Randomisation, intervention delivery and masking

Participants will be randomised (in a 1:1 ratio) to the two intervention arms. Randomisation will be conducted automatically by means of a custom-built secure web service created and managed by the Exeter Clinical Trials Unit (ExeCTU), which interfaces with the trial database, and which will be independent of the trial researchers. To promote balance across key participant characteristics across intervention arms, randomisation will be stratified according to recruitment site (each of the six funded partner universities plus an “other” university category for students recruited elsewhere), and history of depression (no history vs past history of depression – given that this is a strong predictor of future depression and was used previously) [19]. Stratification will be used (on these two variables) and blocking will be used with minimum block size of 4 and maximum block size of 6, occurring at random to maintain concealment.

All the online recruitment and randomisation will be automated and independent of trial researchers. The Exeter CTU EDC system will contact an unblinded team member (administrator/therapist) indicating when an individual [by study ID] has been randomized to the active intervention. This team member will then access the relevant details in the EXCTU database and manually set up the participant in the mobile app intervention using administrator rights via the treatment platform dashboard. An email will also go to the participant indicating the condition to which they are randomised and informing them what to expect. The relevant unblinded team member will also monitor if the participant has accessed the intervention and check if any difficulties and encourage to sign-up.

All assessments will be routinely collected online using the EDC following automated reminders, without the involvement of researchers. Site researchers will be blind to treatment allocation. Site researchers will prompt all participants to complete follow ups by phone and text if they do not respond to the automated email reminders. Any unblinding in contact with a site researcher would be logged as a protocol deviation and only a researcher that remained blind will be able to prompt future follow-up from that participant.

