### Sample size

The sample size was calculated using the primary outcome based on a minimum clinically important difference (MCID) at primary endpoint allowing for power at 0.80 and a two sided alpha at 0.05. The primary outcome is incidence of major depression across the 12 months follow-up. Assuming that the MCID is an absolute risk reduction in incidence of major depressive episodes of 10% based on previously published consensus [55] and that incidence of major depressive episodes will be 25% in the usual practice arm, paralleling previous studies in this high-risk sample [18, 19], and assuming 20% follow-up attrition, then conservatively we require n=324 per arm, giving a total sample required of 648.

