### Statistical analysis plan

The primary analyses will be intention-to-treat (ITT) analyses [56] (i.e. all participants will be included in the analyses according to their randomised allocation) and based on complete case outcome data. The primary inferential analyses will compare across trial arms for the primary and continuous secondary outcomes at 12-months follow up using multilevel mixed-effect models, which enable us to examine nested hierarchies in the data (individual, intervention, university), across time (examining pre-to-post change), to capture dependencies in the data, to investigate individual trajectories (random intercepts, random slopes), and which have less restrictive assumptions re missing data.

Secondary analysis will be undertaken using both Complier Average Causal Effect models and multiple imputation:Complier Average Causal Effect (CACE) analysis [57, 58] to provide an estimate of a treatment effect accounting for pre-specified per protocol adherence and compliance with the treatment, whilst retaining the benefits of randomisation.Multiple imputation following the examination of the pattern of missing outcomes to impute primary and secondary continuous outcomes. Imputation models will be informed by treatment arm, baseline scores, other covariates to be included in the model, and other baseline characteristics found to predict outcome or propensity for missingness (logistic regression models will be used to investigate the associations between baseline characteristics and missingness).

Secondary analyses will be undertaken including:Models will be estimated for the primary and secondary outcomes at 3- and 12-month follow-up and will include the covariates adjusted for in the linear regression models.Cox regression models will be undertaken to investigate between group differences in the time until a major depressive episode.Mediation analyses will be undertaken to gain insight into mechanisms that could explain the potential effect of the interventions on primary outcomes. We will use modern causal inference methods using structural equation modelling or parametric regression models to assess mediation effects [59]. In addition, we will investigate potential moderation of the interventions by site and history of depression.The results of all models will be compared to primary analysis complete case ITT results.Analyses will be undertaken by a statistician blinded to group allocation and using Stata v.17.

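### Coding every control as having received the minimum app dose would invalidate the secondary CACE analysis if carried into it

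*Protocol article*

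**What the plan says.** All references are to the protocol article.

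- **Intervention adherence** (under Interventions) defines a minimum dose of the app, equates compliance with completing at least 2 of its 7 modules, and adds: "All participants in the usual practice control will be defined as receiving the minimum intervention dose".
- **Statistical analysis plan** lists a CACE analysis among the secondary analyses, "to provide an estimate of a treatment effect accounting for pre-specified per protocol adherence and compliance with the treatment", and says that it keeps what randomisation provides. It names no estimator and does not say how controls enter. The adherence section holds the only definition of compliance in the article.
- **Background** (last paragraph) describes the comparator as the ordinary experience of students without the app, and **Study design** gives controls usual practice alone. Under **Randomisation, intervention delivery and masking**, a team member is alerted when someone is allocated to the active arm and then sets that person up in the app by hand.

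**The concern.** A CACE analysis of an intervention offered to one arm needs two facts about controls. Their received dose of the app is whatever they used, presumably none. Whether they would have complied if offered it is unknown. The adherence sentence gives every control a positive value, and that value is wrong whether it is read as dose received or as complier status.

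What is at stake is the validity of the complier estimate. The app is unguided, so partial use is plausible and readers will want to know the effect in those who used it. An estimate built on this coding could point the wrong way, or could report a difference in prognosis between users and non-users as an effect of the app.

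**Working it through.** **Inputs from the documents.** Sample size section: "power at 0.80 and a two sided alpha at 0.05"; "incidence of major depressive episodes will be 25% in the usual practice arm"; an "absolute risk reduction in incidence of major depressive episodes of 10" per cent; "assuming 20% follow-up attrition"; "we require n=324 per arm, giving a total sample required of 648". Allocation is 1:1.

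**Inputs assumed.** The article gives neither the app-arm compliance rate c nor the prognostic gap g, so both are shown as ranges. Here g is the risk without the app in would-be non-compliers minus that in would-be compliers.

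**Step 1: the plan's own figure.** For 25% against 15%, the two-proportion formula gives 250 per arm without and 270 with a continuity correction. 270 × 1.2 = 324 per arm, or 648 in total, which matches. The article gives no figure for the CACE. The intention-to-treat (ITT) effect used below is therefore the design effect, 0.15 − 0.25 = −0.10.

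**Step 2: coding read as treatment received.** The instrumental-variable (Wald) estimator is

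CACE = ITT / (proportion treated in app arm − proportion treated in control arm).

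With controls at 0 the denominator is c. With controls at 1 it is c − 1, which is negative for every c below 1.

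| c | Controls coded 0: −0.10 / c | Controls coded 1: −0.10 / (c − 1) |
|---|---|---|
| 0.4 | −0.250 | +0.167 |
| 0.5 | −0.200 | +0.200 |
| 0.6 | −0.167 | +0.250 |
| 0.8 | −0.125 | +0.500 |

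The reversal does not depend on c; only its size does. At c = 1 the second estimator is undefined. If the ITT effect is zero, both are zero.

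**Step 3: coding read as complier status.** App-arm compliers are compared with the whole control arm. Let r be the risk without the app in would-be compliers and δ the true effect in them. Non-compliers are assumed unaffected by allocation.

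- App-arm compliers: r + δ
- All controls: c·r + (1 − c)(r + g) = r + (1 − c)g
- Difference: δ − (1 − c)g, so the bias is −(1 − c)g

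| c | g = −0.10 | g = 0 | g = 0.05 | g = 0.10 | g = 0.15 |
|---|---|---|---|---|---|
| 0.4 | +0.060 | 0 | −0.030 | −0.060 | −0.090 |
| 0.5 | +0.050 | 0 | −0.025 | −0.050 | −0.075 |
| 0.6 | +0.040 | 0 | −0.020 | −0.040 | −0.060 |
| 0.8 | +0.020 | 0 | −0.010 | −0.020 | −0.030 |

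Negative values favour the app. The bias does not involve δ, so it is present even when the app does nothing.

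**Step 4: check by simulation** (2,000,000 participants, c = 0.6, g = 0.10, true CACE −0.167). The simulated ITT effect was −0.101. The Wald estimate was −0.168 with controls at 0 and +0.253 with controls at 1. Compliers against all controls gave −0.207, against −0.167 − 0.4 × 0.10 = −0.207 from the formula.

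**The case against.** The sentence may mean only that usual-practice students count as adherent to their allocation. As a per-protocol label that is harmless. It stands under adherence, not under analysis, and the CACE paragraph does not repeat it. The separate statistical analysis plan is not at hand and may define the exposure properly. This part of the objection stands, and it makes the point conditional. It does not clear the sentence, which says that controls received the dose, defines that dose in app modules, and sits with the only compliance definition to which the CACE paragraph can refer.

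A reader might infer more than the article supports in three ways:

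- **That the CACE will come out with the wrong sign.** This needs an instrumental-variable estimator with controls entered as treated, and the article names no estimator. All models are also to be compared with the primary ITT results, so a reversed sign would be noticed. The selection bias in step 3 would be harder to spot, because a complier effect is expected to be larger than the ITT effect anyway.
- **That students who finish modules have a better prognosis.** Nothing in the article shows this. The gap could be zero or run the other way, which is why the table includes both.
- **That controls cannot get the app.** The randomisation section points that way, but Baseline and follow-up assessments speaks of signing randomised participants up to the relevant variant of the app. Zero use in controls is the expectation, not an established fact.

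**Conclusion.** The concern holds in conditional form. As written, the control rule conflicts with a valid CACE analysis and with the article's claim that the analysis keeps the protection of randomisation.

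Used as treatment received in an instrumental-variable estimator, it reverses the sign for any compliance below 100%. With the design effect of −10 points, that means +17 to +50 points for c from 0.4 to 0.8, where −25 to −12.5 is right. Used as complier status, it adds a bias of (1 − c) × g towards the app: 5 points at c = 0.5 with an assumed 10-point gap (half the minimum important difference), nothing with no gap, and a bias against the app if g is negative. The sizes rest on assumed values of c and g; the two formulas do not.

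This should be fixed, but it is not critical. CACE is a secondary analysis. The primary ITT analysis, the sample size and data collection are unaffected, so nothing here supports doubt about the main result.

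**What to change.** Replace the sentence on controls with a rule for the CACE analysis along these lines: app dose received is recorded app use in both arms, expected to be zero under usual practice; whether a control would have reached the minimum dose is treated as unobserved; randomised arm is the instrument, in an instrumental-variable or principal-stratification model. With no app use among controls, the Wald denominator is then the app-arm proportion completing at least two modules. If a label for controls as adherent to allocation is wanted, confine it to a separate per-protocol description and state that it does not enter the CACE.

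The cost is a one-sentence rewording in the protocol, carried through to the statistical analysis plan. No data change is needed, since app use and module progress are already to be recorded.

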### Outcomes

Outcomes will be assessed at baseline (pre-randomisation) and 3 months and 12 months post-randomisation.

#### Primary outcome

The primary outcome measure will be the incidence of major depression over 12 months (primary endpoint), indexed by the LIDAS [42] assessing diagnosis retrospectively across the follow-up period.

#### Secondary outcomes

Secondary outcomes include: the Patient Health Questionnaire-9 (PHQ-9), a well-validated measure of depression [43] and the Warwick -Edinburgh Mental Wellbeing Scale (WEMWBS) [44], a widely used and well-validated measure of wellbeing. The Generalized Anxiety Disorder-7 (GAD-7) questionnaire will be used to assess anxiety symptoms [45]. The Work and Social Adjustment Scale (WSAS) [46] will be used to measure functioning with respect to work/education, home management, social leisure, private leisure, and close relationships each rated from 0 not at all impaired to 8 severely impaired. A bespoke questionnaire will assess the use of university-based and non-university-based healthcare (including National Health Service) services, resources, and support. Another bespoke questionnaire will ask participants to report on the actual academic marks and their academic targets for the previous year and whether they were satisfied with their academic progress. The Brief Resilience Scale is a brief and reliable means to assess the ability to bounce back from stress [47]. The Perceived Stress Scale-4 is a four-item measure of individuals perceived levels of stress and ability to cope [48]. The Adverse Events Questionnaire is a brief measure designed to assess stressful events in young people, which is proven to predict subsequent depression [49]. It consists of 3 questions asking about relevant adverse experiences (bad experiences concerning academic study; bad experiences concerning relationships; other bad experiences) rated from 0 “No”, 1 “yes, happened once”, 2 “yes happened twice”, 3 “yes, happened more than twice”. A fourth item asks about minor problems or hassles ranging from 0 “minor problems” to 4 “large number of minor problems and hassles”.

Participants will be asked to complete brief measures each week for eight weeks after randomisation to provide potential mediators of change: a two-item measure of depression (PHQ-2) [50]; a two-item measure of anxiety (GAD-2) [51]; a single item measure of stress over the last week (scored 0 none to 4 very severe); six items from the Cognitive and Behavioural Response to Stress Scale [52] assessing the frequency and usefulness of use of cognitive reinterpretation, behavioural activation, and relaxation or meditation strategies; 3-item adaptations of the automaticity component of the Self-Report Habit Index [53] focused on assessing the extent to which worry and problem-solving respectively are each a habit (e.g., “something that I do automatically" “I do without thinking”) over the past seven days; 2-items from the Self-Compassion Scale-short-form [54]; 2 items from the RRS-Brooding 5-item questionnaire [40]; a one-item measure assessing self-efficacy (“In the last seven days I feel better prepared to handle situations I could not handle before” rated using a seven‐point Likert scale ranging from −3 (“absolutely not true), 0 (“neither nor”) to +3 (“absolutely true”) and a one-item measuring problem clarification (“In the last seven days, I understand myself and my problems better” rated using a seven‐point Likert scale ranging from −3 (“absolutely not true), 0 (“neither nor”) to +3 (“absolutely true”).

The following descriptive variables will be assessed only at baseline: age, gender, sexuality, year of study, course of study, family’s occupational status, country of birth.

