**Methods:**

An online single blind, two-arm parallel-group Randomised Controlled Trial (RCT) to examine the incidence of major depression and symptoms of anxiety and depression across 12 months in university students aged over 16 who screen into the study with self-reported high levels of worry and/or rumination and no current diagnosis of major depression. Eligible participants will be randomised to the active intervention arm (usual practice plus using a self-guided mobile app targeting RNT) or to the control arm (usual practice). In total, 648 participants aged over 16, with no current major depression, bipolar disorder or psychosis will be recruited from UK universities. Assessments will take place at baseline (pre-randomisation), 3 months and 12 months post- randomisation. Primary endpoint and outcome is incidence of major depression as determined by self-reported diagnostic criteria at 12-month follow-up. Depressive symptoms, anxiety, well-being, health-related quality of life, functioning and academic outcomes are secondary outcomes. Compliance, adverse events, and potentially mediating variables will be carefully monitored.

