### Baseline and follow-up assessments

The baseline assessment will take place after electronic informed consent to participate in the trial is provided and consists of web-based self-report measures to assess current and lifetime history of depression, current wellbeing, symptoms of anxiety and depression, social and work functioning, use of services and treatment received, academic grades, resilience, and stressful events, and levels of RNT (see outcome measures and Tables 1 and 2). The Lifetime Depression Assessment Self-report questionnaire (LIDAS) [42] will be used to assess lifetime major depression (MDD) diagnosis according to DSM criteria and is largely based on the widely used Composite International Diagnostic Interview (CIDI). It has been proven to be effective for determining history of depression through self-report in an online digital format, matching the needs for the current study [42]. It consists of a conditional sequence of pre-programmed questions assessing all the diagnostic criteria for depression, with logic cut-outs so that subsequent questions are determined by prior questions, keeping the assessment brief.

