			**Follow-up (months)**	
**Web Assessment**		**Baseline**	**3**	**12**
Pre-screening	date of birth, self-reported mental health	✓		
Informed Consent		✓		
Socio-demographics	Age, sex, employment status, ethnicity, historic mental health problems	✓		
LIDAS	Incidence of current and past major depressive episode (primary outcome)	✓	✓	✓
Rumination	RRS-Brooding questionnaire; secondary outcome	✓	✓	✓
Worry	PSWQ questionnaire; secondary outcome	✓	✓	✓
Wellbeing	WEMWBS questionnaire; secondary outcome	✓	✓	✓
Depression	PHQ-9 questionnaire; secondary outcome	✓	✓	✓
Anxiety	GAD-7 questionnaire; secondary outcome	✓	✓	✓
Resilience	BRS questionnaire; secondary outcome	✓	✓	✓
Perceived Stress	PSS-4 questionnaire; secondary outcome	✓	✓	✓
Stressful Events	ASQ questionnaire; secondary outcome	✓	✓	✓
Use of mental health services and resources			✓	✓
Academic Outcomes		✓	✓	✓

Once consented participants have completed the baseline assessment, they will be randomised automatically by an independent computer system. Randomised participants will be informed of their randomisation allocation and signed up to use the relevant variant of the app via clinically trained members of the research team. The participant’s University email address is used for app set-up.

All participants will be followed up electronically at 3 months and 12 months post-randomisation. At each follow-up point, participants will be automatically sent emails and texts with links to enter their data into the EDC. Each assessment point will involve an automated weekly follow- up by email and then text and telephone follow-ups to participants who haven’t yet completed the EDC assessment at 3 months and 12 months. Tables 1 and 2 give an overview of all measurements. Figure 1 gives an overview of trial flow. Project researchers will be blind to treatment allocation but will be available to participants to answer queries about the trial or the assessments. Participants will receive honorariums for the completion of each of the brief mediator assessments occurring each week for 8 weeks post-randomisation, 3-month and 12-month follow-up assessments.

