### Interventions

#### Usual practice control

This control is what usual practice the participants may receive during the course of the 12-month follow-up. Usual practice, as received by the university student outside of the trial, may include no provision of intervention, local provision of intervention, support from their GP/family doctor, local health services or youth services, or provision of intervention within their university (e.g., well-being service; support and welfare staff). The nature of usual practice will be monitored and assessed by questionnaires at each follow-up assessment, determining what treatment and services participants have received since the last assessment.

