### Trial status

The Trial was registered in ISRCTN, number of identification 86795807. Date of registration: 27 October 2022. Recruitment commenced in July 2023 and is ongoing.

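### As described, the academic item looks back a year at every visit, so at 3 months it asks mostly or wholly about study done before randomisation

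*Protocol article*

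**What the plan says.** The abstract of the protocol article states that "health-related quality of life, functioning and academic outcomes are secondary outcomes". The Secondary outcomes section describes a bespoke questionnaire in which students "report on the actual academic marks and their academic targets for the previous year and whether they were satisfied with their academic progress". This is the only recall period given for marks, and nothing suggests different wording at follow-up.

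The Outcomes section says "Outcomes will be assessed at baseline (pre-randomisation) and 3 months and 12 months post-randomisation", and in Table 2 the row "Academic Outcomes" is ticked in all three columns. Baseline and follow-up assessments lists "use of services and treatment received, academic grades, resilience, and stressful events" among the baseline measures, so marks are already held before randomisation. The Statistical analysis plan section then says "Models will be estimated for the primary and secondary outcomes at 3- and 12-month follow-up", without excepting the academic outcome. Trial status records "Recruitment commenced in July 2023 and is ongoing", and no restriction of entry to one part of the academic year is stated.

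The questionnaire on usual practice is framed differently. It is described under Usual practice control as "determining what treatment and services participants have received since the last assessment".

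**The concern.** A follow-up outcome should describe a period in which the intervention could have acted. A one-year look-back asked 3 months after randomisation reaches well back behind randomisation, and the app cannot change marks already earned. To that extent the 3-month comparison sets two randomised groups side by side on something close to their baseline values.

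The stake is interpretive. The Background names poorer academic results among the harms of poor student mental health. A 3-month difference near zero could be read as evidence of no academic benefit when the item had little chance of showing one. The same question arises at 12 months, but there the answer depends on what kind of year is meant.

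**Working it through.** The article gives no figure to reproduce. The check is the share of the look-back window that falls before randomisation at visit month T. It measures time in the window, not the number of marks.

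**Inputs from the article:** a one-year recall period (Secondary outcomes); visits at T = 3 and T = 12 (Outcomes, Table 2).

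**Assumed, because the article does not say:** whether the year is a rolling 12 months or an academic year. For the academic-year readings I also assume a 1 September start and L = 9 or 10 teaching months. Entry is taken at r = 0 to 11 months after 1 September.

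**Formulas**
- Rolling year: share = max(0, 12 − T)/12.
- Academic year starting at month s: share = max(0, min(s + L, r) − s)/L. For the most recently completed year, s is the latest multiple of 12 with s + L ≤ r + T. For the year before the current one, s = 12 × (floor((r + T)/12) − 1).

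**Rolling year**
- T = 3: (12 − 3)/12 = 75%.
- T = 12: (12 − 12)/12 = 0%.

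**Academic-year examples, L = 9**
- Entry 1 November (r = 2), T = 3: the most recently completed year has s = −12 and ended at month −3, before entry. Share = 9/9 = 100%.
- Entry 1 March (r = 6), T = 3: the most recently completed year has s = 0. Share = 6/9 = 67%.
- Entry 1 November (r = 2), T = 12: the most recently completed year has s = 0. Share = 2/9 = 22%.
- Entry 1 June (r = 9), T = 12: the most recently completed year has s = 12, share 0%. The year before the current one has s = 0, share 9/9 = 100%.

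**All 12 entry months, L = 9 and 10**

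| Reading | Month 3 | Month 12 |
|---|---|---|
| Rolling 12 months | 75% | 0% |
| Most recently completed academic year | 67–100%; 100% for 9 of 12 entry months | 0–90%; above 0 for 8 or 9 of 12 entry months; never 100% |
| Academic year before the current one | 90–100% | 0–100%; above 0 for 11 of 12 entry months; 100% only for entry after teaching ends |

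On either academic-year reading, the 3-month form covers the same academic year as the baseline form for 9 of 12 entry months.

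**With the window starting at randomisation or at the preceding assessment:** the share is 0% at both visits.

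**The case against.** The strongest reply is that the instrument itself is not shown. One sentence in a condensed article covers three visits, a one-year look-back is natural at baseline, and the follow-up form may be worded differently. The usual-practice questionnaire shows that the team knows how to anchor a follow-up item. This stands as a reason for modest confidence, but it does not remove the point. The article does state a recall period, and that period does not fit the visit schedule it also states. An analysis plan cannot repair this if the item collects the wrong months.

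Second, the outcome is peripheral. The hypothesis in the Objective section does not mention academic results, the main inferential comparison is at 12 months, and the 3-month models are listed among secondary analyses. This is correct and limits the importance of the point.

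Third, a reader might infer that the 3-month academic comparison is bound to be null. The documents do not support that. On a rolling year 25% of the window follows randomisation, and on the academic-year readings some entry months leave part of the window after it. The satisfaction item is not clearly tied to the one-year period and could move by 3 months.

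Fourth, a reader might infer that a definite fraction of the 12-month effect is lost. The documents do not support that either. A rolling year gives 0% overlap. The academic-year readings give mostly partial overlap, and its extent rests on an entry calendar and result-release dates that the article does not contain. Any percentage would only restate an assumption.

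**Conclusion.** The point holds for the 3-month marks on every reading tried: from about two thirds to all of the period asked about precedes randomisation. The 75% on a rolling year follows from the article's own figures; the academic-year ranges rest on the assumed calendar. The consequence is dilution towards no difference and near-repetition of the baseline value. It works equally in both arms, so it is not bias between them.

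At 12 months the item is sound if the year is a rolling one. If an academic year is meant, which is plausible for marks and targets, the window partly precedes randomisation for some entry months and occasionally does so wholly. The resulting loss cannot be sized from the article.

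This is a minor issue on one secondary outcome. The primary outcome and the sample size are unaffected.

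**What to change.** - Word the follow-up item for the time since randomisation or since the preceding assessment, as the usual-practice questionnaire does, and record the academic year to which each reported mark belongs.
- Do not model marks as an outcome at 3 months. The satisfaction item can stay there, worded for the period since joining the study.
- At 12 months, adjust for the baseline mark. Present an analysis limited to post-randomisation marks as a sensitivity analysis only, and report by arm how many students lack such a mark. Having one is itself determined after randomisation, so making this the main analysis would select on a post-randomisation variable.

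The cost is one reworded bespoke item in the data capture system and a few lines on the analysis. Because recruitment was under way at publication, a change may leave two item versions in one dataset, so the version should be recorded. For forms already returned, the completion date helps to place the academic year but does not show whether that year's results had been released. Some students will have no post-randomisation mark.
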